### Data collection

#### Baseline assessment

Following appropriate consent procedures, baseline (TP0) data will be collected via researcher-led completion of questionnaires, and this will take approximately 30 min. Immediately after, participants will be randomised to the control or intervention arm and informed of their allocation. Participants randomised to the intervention arm will be provided with a face-to-face appointment to meet with their interventionist. This is the process used by the current providers ((VSO)when engaging with individuals in the prison setting. The three telephone sessions will be delivered following release from prison by one of the trained interventionists. In addition to the outcome measures (described below), data on age, gender, marital status, educational status and contact details will be collected.

#### Blinding

Due to restrictions regarding electronic equipment and mobile phone use by researchers while in prison, a randomisation system, such as an interactive voice response telephone system or one accessed over the web, cannot be used. Allocation will be conducted at participant level using random permuted blocks of variable size^3 5 6^ stratified by site using sealed envelopes, based on a predetermined random number allocation carried out by Edinburgh Clinical Trials Unit (ECTU).^27 35^

Researchers will not be involved in delivering the active and control interventions but will be aware of the study allocation of participants as the trial progresses. Allocation concealment will be used whereby neither the person delivering the interventions nor the participant will be aware of the study allocation until they are irrevocably entered into the trial. Both the trial statistician (RP) and health economist (JB) will be blinded to group allocation and will only have details of study participants by study number.

#### Follow-up

Follow-up assessments will be conducted at 6 (TP1) and 12 months (TP2) post recruitment. The original aim was for these to be conducted by the researcher either in person or by telephone. In light of COVID-19 restrictions, follow-up assessments have also been adapted to enable self-completion using hard copies or electronic versions. Where participants are identified as being incarcerated at follow-up, arrangements with the relevant prison will be made to undertake the follow-up. Attempts to contact participants will be multifaceted, including telephone calls, text messages and emails, based on participants’ preferred method of contact, at varying times and days of the week. We will record the number of participants invited to participate; responded; were eligible; recruited; transferred; subsequently sentenced; liberated, and lost to follow-up. The number who returned to prison during the 12 months and who completed the trial will also be recorded.

### Outcomes

#### Primary outcome measure

The proposed primary outcome measure is alcohol consumed, in units where one unit equals 8 g or 10 mL of ethanol, per week will be derived from the frequency and quantity of alcohol consumption questions in the extended version of AUDIT using a formula developed and employed in a number of RCTs of interventions for alcohol consumption.^36 37^ A score of 8+ is referred to as a ‘positive screen’ and indicates drinking at hazardous (score of 8–15), harmful (score of 16–19) or probable dependent level (score of 20+). A score of 8 or more out of a possible 40 on the AUDIT has an established sensitivity of 92% and specificity of 94%^28^ to detect those at risk of harm from alcohol use. The AUDIT will be administered at TP0, TP1 and TP2.

#### Self-report secondary outcomes measures

Secondary outcome measures will be completed at TP0, TP1 and TP2.

The Warwick-Edinburgh Mental Well-being scale (WEMWBS) will be used to assess mental well-being.^38^ This tool uses a 5-point Likert scale, which gives a score of 1 to 5 per question, giving a minimum score of 14 and maximum score of 70. A higher WEMWBS score indicates a higher level of mental well-being.^38^

Readiness to change will be measured using the Readiness to Change Ruler, which measures readiness to change drinking behaviour.^7^

Self-reported alcohol self-efficacy will be measured using the Drinking Refusal Self-Efficacy Questionnaire—Revised (DRSEQ-R)^39^ and alcohol expectancy, using the Negative Alcohol Expectancy Questionnaire (NAEQ).^40^

The EuroQol five-dimensional five-level (EQ-5D-5L) will be used to measure health-related quality of life and is being scoped for potential future use to generate quality-adjusted life years (QALY).^41^ A bespoke public sector service use questionnaire will be adapted based on the Economic Form 90^42^ to determine public sector costs in the domains of health and social care, criminal justice system, unemployment and welfare.

#### Other secondary outcome measures

Attempts will be made to access data from the PNC to collect individual-level data on recidivism rates as measured by ‘proven’ reconviction rates^20^ over 12 months, since TP0. The number of participants incarcerated at TP1 and TP2 will also be recorded.

Individual-level data relating to health and social care use will also be sought. If access is possible, data derived from Community Health Index (CHI)/NHS number at TP3 will be used to validate the bespoke public sector service use questionnaire. Furthermore, data will be collected on the time spent by researchers and practitioners on APPRAISE to inform the resources needed for a definitive RCT.

#### Mechanisms of impact

An intervention logic model (figure 1) informed by Social Cognitive Theory has been developed. The underlying causal mechanisms will be examined to provide increased understanding of how the intervention influences change through the quantitative assessment of key behavioural markers (mediators) of change, that is, self-reported self-efficacy, using the DRSEQ-R^39^ and alcohol expectancy, using the NAEQ.^40^ These behavioural markers of change will be recorded at TP0, TP1 and TP2. An exploratory prognostic analysis will be undertaken to explore the nature of change within these domains and their relationship to the primary outcome. The relationship between alcohol consumption, receipt of the intervention and reoffending will also be assessed. In addition, we will be interviewing 32 men who took part in the study (16 at each site), 8 intervention staff from CGL and 10 additional stakeholders. The qualitative exploration of participant responses to and interactions with the intervention will be undertaken to identify unanticipated pathways and consequences at 12 months of follow-up.

### Data analysis

The progress of participants through the APPRAISE pilot trial will be presented in accordance with the CONSORT (Consolidated Standards of Reporting Trials) guidelines^43^ to allow descriptions of key parameters required for a future RCT; eligibility rates, consent, adherence, retention at follow-up and data completeness of outcome measures.

The statistical analyses will be primarily descriptive, providing an estimate of the proportion of those eligible, consenting, adhering to the intervention and retention rates at 6 and 12 months. These parameters will inform the power calculations for a future RCT and confirm or identify the need for modifications in relation to other aspects of the trial design, particularly the acceptability of study processes and outcome measures to participants and staff. Data about the flow of participants through the APPRAISE pilot trial will include numbers screened, the prevalence of the target condition, numbers providing contact details, numbers eligible and willing to consent and numbers followed up successfully at TP1 and TP2. In addition, data completeness for each of the instruments and any potential bias in the follow-up data will be ascertained.

Analysis of the primary outcome will also provide estimates of the variance within and between groups for exploration of sample size calculations for a definitive RCT. Furthermore, we will calculate the variance of all primary and secondary outcome measures within groups to explore their utility in a definitive study. If access to PNC data is possible, proven reconviction rates will be measured by the number of offences committed by each treated participant against the number committed in the comparison group. Time-to-event analysis will also explore differences in offending patterns.

Calculation of between trial-arm differences (with 95% CIs) will indicate the likely effect sizes that will be observed in a future definitive trial.

For the primary outcome analysis, the mean difference (with 95% CI) in alcohol units consumed between the two randomisation groups will be calculated, both overall and stratified by site. A complete case analysis will be used, but a sensitivity analysis will also be incorporated to explore the effects of missing data. This will involve using multiple imputations for the primary outcome in a supplementary analysis, provided that the valid sample size is sufficient to support this. In addition, we will add and subtract one-unit difference (alcohol units) to the missing data as part of a sensitivity analysis to explore how the 95% CIs change depending on our assumptions about the missing data (bearing in mind that the imputed data cannot be less than zero). This is similar to the sensitivity analysis method suggested in White *et al* (2011) which involves determining how large an amount can ‘*be added to or subtracted from the imputed data without changing the clinical interpretation of the trial’*. We will adopt a similar approach to determine how sensitive the conclusions of the APPRAISE pilot trial (and the decision about whether to proceed with an RCT) are to our assumptions about missing data.

A statistical analysis plan will be written and finalised prior to analysis.

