## Introduction

### Background/Rationale

The prevalence of at-risk drinking, which is defined as drinking at levels that harm a person’s health, is far higher among those within the criminal justice system (73%)^1–5^ than the general population (35%).^6^ In the United Kingdom (UK), between 51% and 83% of incarcerated people are classified as risky drinkers,^7^ and for those on remand in prison, the prevalence is between 62% and 68%.^5^ Furthermore, alcohol dependence among those incarcerated (43%) is 10 times higher than the general population.^5^ The impacts of risky drinking are significant, resulting in significant health, economic and social burden on individuals, families and society as a whole.^8^ Addressing alcohol harm in prisons, at what can be considered a ‘teachable moment’, could reduce the risk of reoffending, reduce costs to society and help address health inequalities.^9^

There is currently robust evidence from systematic reviews and meta-analyses, indicating that alcohol brief interventions (ABIs) are effective in reducing alcohol consumption among at-risk drinkers in healthcare settings.^8 9^ However, there is little evidence of the effectiveness of ABIs in reducing risky drinking among those incarcerated, particularly those on remand,^10 11^ despite there being evidence in the UK that ABIs can reduce recidivism.^12^

In addition, ABIs have been shown to reduce recidivism within the probation setting.^13^ Our systematic review of the efficacy of psychosocial alcohol interventions for incarcerated people^10^ found that interventions within prison have the potential to impact alcohol use positively; however, because of small numbers and different outcome measures, it was not possible to conduct a meta-analysis or generalise findings. Notably, none of the studies focused on men on remand, with remand referring to individuals who are unconvicted or convicted and unsentenced, held in custody awaiting trial and/or sentencing. The intervention in this proposed study builds on previous research exploring the theoretical validity of a self-efficacy enhancing ABI.^14 15^ This intervention was initially tested within a pilot cluster randomised controlled trial (RCT), in a general hospital setting, and provided evidence of a potential effect.^15^

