### Sample size

A total of 180 adult men (18 years and over) on remand will be recruited from two sites: one within the Scottish Prison Service (SPS) (n=90); and the second from Her Majesty’s Prison and Probation Service (HMPS) in England (n=90). These sites were purposively selected following PRISM-A, as they offer geographical, socioeconomic and ethnic diversity, along with differing procedures and structures.^16^ Both prisons provide alcohol services via external agencies who engage with people in custody and following release. Prisons have varying induction procedures, communication mechanisms and processes, and available, secure space to engage participants. Understanding the different approaches and dynamics will be important when designing a future RCT.

The target population is men on remand in prison, who have been in prison for 3 months or less. The average time on remand is approximately 9 weeks in England^22^ and 4 weeks in Scotland.^23^ We estimate that approximately 50% of participants will be released, while the rest will remain incarcerated; leaving 45 participants per study arm (90 in total) across the two sites.

This sample size was calculated to take account of the following factors^24^:

It will enable calculations of two-sided 95% CIs around proportions recruited, released and dropout in each study arm with half-widths of less than 0.15.It exceeds the 30 per group recommendation of Lancaster *et al*^25^ and 35 participants per group recommendation of Teare *et al*^26^ for estimating key unknown design parameters, for example, SD with sufficient precision with a continuous primary outcome.It will ensure that within each arm, across each site, we satisfy the minimum 12 per group ‘rule of thumb’ outlined by Julious^27^ for pilot trials.

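### The 12-month reconviction measure starts in custody, has no time-at-liberty denominator, and leaves its event date and comparison group loosely worded, so the rate meant for trial planning is diluted and ambiguous

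*Protocol article*

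**What the plan says.** All references are to the protocol article.

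- **Window.** Under Other secondary outcome measures, proven reconviction is measured "over 12 months, since TP0".
- **Start of the window.** Under Baseline assessment, "baseline (TP0) data will be collected via researcher-led completion of questionnaires". Randomisation follows at once, so TP0 is in effect the randomisation date, inside prison.
- **Legal status at that point.** The Background defines "remand referring to individuals who are unconvicted or convicted and unsentenced, held in custody awaiting trial and/or sentencing".
- **Expected release.** Under Sample size, "We estimate that approximately 50% of participants will be released, while the rest will remain incarcerated". The same paragraph says "The average time on remand is approximately 9 weeks in England" and gives about 4 weeks for Scotland.
- **Measure and comparison.** Under Data analysis, if Police National Computer (PNC) data can be obtained, "proven reconviction rates will be measured by the number of offences committed by each treated participant against the number committed in the comparison group". A time-to-event analysis of offending is added, with no time origin given.
- **Related analysis.** Under Mechanisms of impact, "The relationship between alcohol consumption, receipt of the intervention and reoffending will also be assessed".
- **Uptake.** Progression criterion 4c asks for at least 70% of the intervention arm to receive one session or more.
- **Custody data.** Numbers sentenced, liberated, returned to prison, and incarcerated at 6 and 12 months are recorded. No use of them as exposure time is described.

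**The concern.** Three features of the stated measure fit this population poorly.

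1. **Exposure.** The clock starts in custody, and about half the men are expected to stay there. A 12-month offence count from TP0 mixes time with and without the opportunity to offend in the community. The section presents between-arm differences as a guide to the effect sizes of a definitive trial, and outcome variances as a guide to each measure's usefulness. A rate that is largely custody time serves those purposes badly unless time at liberty is shown beside it.
2. **Event date.** One section speaks of reconviction within the window and the other of offences committed. If events are dated by conviction, a conviction on the index charge after TP0 counts as reconviction for an offence that predates randomisation. If they are dated by offence, it does not.
3. **Comparison.** Setting *treated* participants against a comparison group, read literally, drops men who were allocated to the intervention but never received a session. That group could be up to 30% of the arm with criterion 4c still met.

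**Working it through.** **The plan's own figure.** The article states no event rate or sample size for reconviction. Its only related figure is the general precision statement, which reproduces: the 95% half-width at p = 0.5 with 45 per arm is 1.96 × √(0.25/45) = 0.146, below the stated 0.15. Those 45 per arm already rest on the 50% release share.

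**Step 1: share of the window at liberty.** Inputs from Sample size are 50% released and mean remand of 4 weeks (Scotland) and 9 weeks (England). Two assumptions are added: men not released stay in custody for all 52 weeks, and released men leave one mean remand stay after TP0.

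Share at liberty = released share × (52 − weeks held)/52.

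| Released share | Scotland | England |
|---|---|---|
| 40% | 0.4 × 48/52 = 37% | 0.4 × 43/52 = 33% |
| 50% | 0.5 × 48/52 = 46% | 0.5 × 43/52 = 41% |
| 60% | 0.6 × 48/52 = 55% | 0.6 × 43/52 = 50% |

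At 50% released, release on the day of TP0 would still give only 50%. Return to custody would lower every figure. If instead the held half left at 6 months, 0.5 × 26/52 = 25 percentage points would be added, giving about 71% and 66%.

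If no proven offences arise in custody, a 12-month rate in the base case is 46% or 41% of the rate per year at liberty. At the same at-liberty rate, the English site would show 43/48 = 90% of the Scottish figure.

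**Step 2: what dilution does to planning.** Assume 12-month reoffending of 40% against 32% among released men and none among men held. With half released, the all-randomised rates are 20% against 16%.

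For 80% power at two-sided 5%, n per arm = [1.96√(2p̄(1−p̄)) + 0.842√(p₁(1−p₁) + p₂(1−p₂))]² / (p₁−p₂)².

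- Released men only: p̄ = 0.36, difference 0.08, n = 564 released men.
- All randomised: p̄ = 0.18, difference 0.04, n = 1447.

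The two are not directly exchangeable. Obtaining 564 released men per arm means randomising about 564/0.5 = 1128, and the released-only contrast is no longer a comparison of randomised groups. With base rates of 30% to 60% among released men and the same relative reduction, the pairs run from 859 and 2036 down to 270 and 859.

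**Step 3: if index convictions were counted.** Assume true rates of 20% and 16%, and a share q convicted on the index charge after TP0, equal in both arms and independent of new offending. The any-conviction rate is 1 − (1−q)(1−r), so the 4-point difference becomes (1−q) × 4 points: 2.8 at q = 0.3, 2.0 at q = 0.5 and 1.2 at q = 0.7.

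**Step 4: if *treated* were applied literally.** Take 70% uptake and no true effect, with assumed rates of 35% in men who attend and 50% in men who do not. The control rate is then 0.7 × 0.35 + 0.3 × 0.50 = 39.5%, and the treated-only contrast shows 35 − 39.5 = −4.5 points. With 40% in attenders the control rate is 43%, and the contrast is −3.0 points.

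Only the 50%, 9 weeks, 4 weeks and 70% come from the article. The rates in Steps 2 to 4 are illustrations.

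**The case against.** The strongest reply is that this is wording, not error, and most of it belongs in the statistical analysis plan that the article promises. Four stronger readings are tempting, and the document supports none of them.

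- **That index convictions are counted.** The Data analysis text counts offences committed, and an index offence precedes TP0, so on that reading it is excluded. The source cited for *proven* reconviction is not available here. The point is an ambiguity.
- **That randomisation is broken.** This hangs on the one word *treated*. No as-treated set is defined, the same section goes on to speak of differences between trial arms, and the primary outcome is compared between the randomised groups. The analysis of intervention receipt sits with the exploratory mechanism work. The 70% in criterion 4c is a progression threshold, not an exclusion rule.
- **That custody time biases the comparison.** TP0 immediately precedes randomisation, so custody time is balanced between arms in expectation. Randomisation is stratified by site, so unequal time at liberty by site does not confound the arms.
- **That the time-to-event clock starts at TP0.** No origin is stated for that analysis.

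It is also fair that the article gives no horizon for remaining incarcerated, and that men may already have served up to 3 months, so a mean total stay is only a rough guide to time remaining after TP0. Reconviction enters no progression criterion, and objective 1e asks only whether the data can be accessed.

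What stands is what the article itself fixes: a window opening in custody, a count of offences with no exposure measure, two descriptions of the event that do not agree, and a comparison phrase that does not match the rest of the section.

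**Conclusion.** The point holds as one of dilution and ambiguity. If half the men stay in custody for the full year and the rest leave one mean remand stay after TP0, about 46% of the window in Scotland and 41% in England is at liberty, or 33% to 55% across release shares of 40% to 60%. The share rises if the men held leave within the year. A raw 12-month rate would then understate the at-liberty rate by about half, and somewhat differently by site, while leaving the randomised contrast unbiased.

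The event-date rule and the word *treated* could each distort the result if resolved the wrong way, but the text does not show that they will be. It would also be too strong to say that the outcome could not inform a definitive trial: data access, completeness and all-randomised rates would still do so. This is a should-fix point on an exploratory secondary outcome that depends on data access.

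**What to change.** 1. In Data analysis, replace *each treated participant* with *each participant allocated to the intervention arm*.
2. Count proven offences with an offence date after TP0, and exclude the index charge explicitly.
3. Keep the all-randomised 12-month comparison from TP0 as the main result.
4. Report days at liberty by arm and site.
5. As supplementary descriptive analyses, give offences per person-year at liberty (a count model with log time at liberty as offset and site as covariate) and time to first offence from first liberation.

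The cost is small: rewording, offence dates in the PNC request, and release and return-to-custody dates for both arms, where the article already plans to record the numbers liberated and returned. The at-liberty analyses condition on an event after randomisation, so they may stand beside the all-randomised result but not replace it.

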**Methods and analysis:**

APPRAISE will use mixed methods, with two linked phases, across two prisons in the UK, recruiting 180 adult men on remand: 90 from Scotland and 90 from England. Phase I will involve a two-arm, parallel-group, individually randomised pilot study. The pilot evaluation will provide data on the likely impact of A two-arm parallel group individually randomised Prison Pilot study of a male Remand Alcohol Intervention for Self-efficacy Enhancement (APPRAISE), which will be used to inform a future definitive multicentre RCT. Phase II will be a process evaluation assessing how the ABI has been implemented to explore the change mechanisms underpinning the ABI (figure 1) and to assess the context within which the ABI is delivered.

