#### Objective 4: to assess whether operational progression criteria for conducting a future definitive RCT are met across trial arms and study sites and if so, develop a protocol for an RCT. *Operational progression criterion are based on previous research results*^3^

4a. Do the two prisons invited to the study agree to take part?

4b. Based on knowledge from previous data, do at least 90 eligible participants consent to take part and be randomised?

4c. Do at least 70% of participants allocated to the intervention condition go on to receive at least one intervention session?

4d. Do at least 60% of participants take part in the follow-up assessments at 12 months across trial arms and study sites?

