## Methods and analysis

### Study design

The study aligns to the MRC framework^19^ using mixed methods within two linked phases conducted across two sites.

Phase I will involve a two-arm, parallel-group, individually randomised pilot study (Objectives 1 and 4). The pilot evaluation will provide data on feasibility and an assessment on the likely impact of the ABI to inform the feasibility and design of a future RCT.

Phase II will comprise a process evaluation (Objectives 2 and 3), drawing on the MRC process evaluation framework to guide the planning and design of the evaluation.^21^ The aim of the process evaluation is: to assess how the ABI is implemented; to undertake a preliminary exploration of the change mechanisms underpinning the intervention (figure 1), and assess the delivery context of the ABI.

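### The plan says the pilot's arm differences will indicate the effect sizes of the definitive trial, but the pilot was not sized to estimate an effect and its interval is too wide to predict one

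*Protocol article*

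**What the plan says.** The sentence at issue closes the general part of the Data analysis section: "Calculation of between trial-arm differences (with 95% CIs) will indicate the likely effect sizes that will be observed in a future definitive trial". Two other places prepare for it. The Study design section says that Phase I will give "an assessment on the likely impact of the ABI to inform the feasibility and design of a future RCT", and the abstract says "The pilot evaluation will provide data on the likely impact of" the intervention, as an input to the later multicentre trial.

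The Sample size section has a narrower purpose. It states "A total of 180 adult men (18 years and over) on remand will be recruited from two sites" and expects about half to be released, "leaving 45 participants per study arm (90 in total) across the two sites". It then gives three reasons for the number: "two-sided 95% CIs around proportions recruited, released and dropout in each study arm with half-widths of less than 0.15"; exceeding published per-group recommendations for estimating unknown parameters such as an SD; and a minimum of 12 per arm within each site. None of these concerns the precision of an arm difference.

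Objective 1b names what the pilot should supply for the later sample size: the SD of candidate continuous outcomes, and the recruitment, retention and follow-up rates. Effect size is not on that list. Objective 4 sets four operational progression criteria, one of which is "Do at least 60% of participants take part in the follow-up assessments at 12 months across trial arms and study sites". None of the four uses an outcome difference.

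**The concern.** The sentence makes a positive, unqualified claim about what the pilot difference will show, and the design was not built to support it. A colleague planning the next trial could take it as licence to use the observed difference as the target difference. When the estimate is high by chance, a trial sized that way is too small. When it is low or has the wrong sign, the intervention may look not worth pursuing.

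The decision to proceed is also touched. The last part of Data analysis says that the missing-data sensitivity analysis of the alcohol outcome will show how robust both the pilot's conclusions and the decision to go on to a full trial are. That links the outcome result to progression, although the criteria under Objective 4 do not.

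**Working it through.** **Inputs from the protocol.** 180 randomised in two arms. Equal allocation is implied by 45 per arm but not stated, so 90 per arm. Expected number released: 45 per arm. Follow-up floor at 12 months: 60%, so 0.60 × 90 = 54 per arm. Two-sided 95% intervals. Primary outcome: mean difference in weekly alcohol units between the randomised groups, complete cases.

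**Assumptions not in the protocol.** True standardised effect d of 0.2, 0.3 or 0.5 SD; approximately normal estimates; a later trial with two-sided 5% significance and a 90% power target. The protocol gives no SD, target difference, significance level or power for the later trial.

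**Step 1: the plan's own figure.** Worst-case half-width for a proportion at 45 per arm: 1.96 × √(0.25/45) = 0.146. This is below 0.15, so the stated precision reproduces.

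**Step 2: precision of the arm difference.** Half-width in SD units = t(0.975, 2n−2) × √(2/n).

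| n per arm | Basis | Calculation | Half-width |
|---|---|---|---|
| 90 | no loss | 1.973 × 0.149 | 0.29 SD |
| 54 | 60% of 90 | 1.983 × 0.192 | 0.38 SD |
| 45 | expected released | 1.987 × 0.211 | 0.42 SD |

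For example, an observed 0.30 SD at 54 per arm has a 95% CI of 0.30 ± 0.38, that is −0.08 to 0.68 SD. This is compatible with no effect and with a large one.

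**Step 3: contrast with the SD.** Under normality, the 95% CI for the pooled SD at 45 per arm runs from about 0.87 to 1.17 times the estimate. The design serves the aim in Objective 1b much better than the aim of predicting an effect.

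**Step 4: what would follow if the later trial were sized on the pilot estimate.** Let the estimate be e, with standard error √(2/n). The per-arm size would be N = 2 × (1.960 + 1.282)²/e², and true power is Φ(d√(N/2) − 1.960). True power is below 80% when d × 3.242/e < 2.802, that is, when e > 1.157d. At n = 54 the standard error is 0.192, so:

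- P(true power below 80%) = 1 − Φ(0.157d/0.192)
- P(wrong sign) = Φ(−d/0.192)

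| True d (assumed) | Wrong sign | Below 80% power, of all pilots | Mean true power if e > 0 |
|---|---|---|---|
| 0.2 | 15% | 44% | 71% |
| 0.3 | 6% | 40% to 41% | 78% |
| 0.5 | 0.5% | 34% | 84% |

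The last column is from simulation. The simulation also allows for the pooled SD being estimated, and it agrees with the closed forms in the other two columns to within about half a percentage point.

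**The case against.** The strongest reply is that the main harm is not in the plan. Nowhere does the protocol say that the definitive trial will be sized on the observed difference. Objective 1b lists the SD and the rates. In Data analysis, the parameters said to feed the power calculations are eligibility, consent, adherence and retention, and the primary outcome contributes variances. The progression criteria contain no effect. The analyses are called mainly descriptive, and 95% CIs are specified, which show the uncertainty to anyone who reads them.

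Most of this stands. A reader might infer that the plan commits to powering the next trial on the pilot effect, or to dropping the intervention if that effect is small. The documents support neither inference, so the figures in Step 4 show what a misuse would cost and do not describe a planned procedure.

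A reader might also combine the 60% floor with the 45 expected to be released, giving 27 per arm and a still wider interval. That assumes an analysis limited to released men. The protocol compares the randomised groups, arranges follow-up in prison where needed, and applies the 60% to participants generally. In addition, 60% is a floor for progression and not an expected rate.

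Nor can one say that the interval reaches from worthwhile benefit to worthwhile harm, because no worthwhile difference is defined and the limits depend on the estimate.

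What the reply does not remove is the sentence itself. Reporting the differences with intervals is sound; the predictive interpretation attached to them is not.

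**Conclusion.** The point holds as a fault in a stated claim. The half-width is at least 0.29 SD even with complete follow-up, so the conclusion does not depend on attrition. At the protocol's own follow-up floor it is 0.38 SD. The half-widths depend only on the sample size and equal arms, with the usual large-sample approximation for an outcome that is bounded at zero and probably skewed.

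The consequences for a later trial are conditional on someone using the estimate as the target, and on the assumed effects of 0.2 to 0.5 SD. The risk of an underpowered trial persists across that range (44% falling to 34%), whereas the wrong-sign risk depends strongly on the true effect (15% falling to 0.5%). The pilot itself is not invalidated. The correction should be made because the claim and its supporting wording appear in three places, and the remark about the decision to proceed adds a link that the progression criteria do not contain.

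**What to change.** In Data analysis, replace the sentence with a statement that arm differences and their 95% CIs are descriptive and will set neither the target difference of the definitive trial nor the decision to proceed, which rests on the operational criteria under Objective 4.

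State that the target difference will be a prespecified minimum important difference in units per week. State also that the pilot will supply the SD, with allowance for its uncertainty, and the recruitment, retention and follow-up rates, as Objective 1b already intends. A fixed inflation factor for the SD based on normal theory is not advised, since weekly units cannot fall below zero and are probably skewed.

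Align the wording on likely impact in the abstract and Study design, and the remark on the decision to proceed in the missing-data paragraph.

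The cost is text only: no change to recruitment, data collection or the planned calculations. The downside is a more modest claim for the pilot.
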